#### Statistical analyses

Descriptive statistics will be used, and data will be summarized using mean, standard deviations, and percentiles. Normality of data distribution will be tested using the Kolmogorov-Smirnov test. Normal variables and comparison among three groups (massage with stretching, relaxation and imagination therapies, and dental treatment) will be assessed at baseline, immediately after treatment and at 2-month follow-up using Analysis of Variance. Post-hoc tests will consist of the Turkey test for parametric variables, and the Dunn’s test for non-parametric variables. Analyses will be conducted using SPSS 19 and SigmaStat 3.5. A level of significance of 5% will be used.

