### Sample size calculation

Sample size was defined in order to detect a 2-point difference between groups on the pain intensity outcome measured by the Visual Analogical Scales*,* assuming a standard deviation of 2 points. Power was defined as 80% for an alpha of 5% and attrition (drop-outs) of 20%. Accordingly, 24 participants per group will be needed.

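### A normality pre-test on the trial data chooses between mean-based and rank-based analysis, and its application is not fixed, so the effect measure for one outcome may differ between visits

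*Protocol article*

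**What the plan says.** Under Statistical analyses the protocol article states: "Normality of data distribution will be tested using the Kolmogorov-Smirnov test". Variables found normal are then compared among the three groups; these comparisons "will be assessed at baseline, immediately after treatment and at 2-month follow-up using Analysis of Variance". The follow-on comparisons split the same way: "Post-hoc tests will consist of the Turkey test for parametric variables" (Tukey is evidently meant), while Dunn's procedure is the "test for non-parametric variables". The level is given once: "A level of significance of 5% will be used".

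No if-then sentence is written, but the section gives the normality test no other purpose than to sort variables into these two branches. It does not state the level of the pre-test, its critical values, whether it is applied per group, pooled or to residuals, or whether a variable is classified once or at each visit.

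The Sample size calculation section is on the mean scale: "Sample size was defined in order to detect a 2-point difference between groups on the pain intensity outcome", with an SD of 2 points and 20% attrition, giving 24 per group. The Study aim section hypothesises a larger pain reduction after treatment that is still present at 2 months.

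**The concern.** When a test on the outcome data selects the confirmatory method, the quantity being compared is not known until the data are in. ANOVA with Tukey compares means; Dunn's test compares mean ranks and gives no estimate of a 2-point VAS difference. Nothing in the text ties an outcome to one branch across visits.

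There is a reason to expect the shape of the pain data to change. Entry requires a VAS of at least 3, so baseline is cut off from below. Later visits are not, and on a scale that ends at 0 they may pile up at the floor. If the classification were repeated at each visit, the post-treatment and 2-month results for pain could be reported on different scales. The hypothesis of a maintained benefit would then rest on two unlike comparisons.

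**Working it through.** **Inputs from the article.** 24 per group, 72 in total, 20% attrition; difference 2, SD 2, 80% power, alpha 5%; VAS on a 10 cm scale; entry VAS at least 3. Completers: 24 × 0.8 = 19.2, about 19 per arm; 72 × 0.8 = 57.6, taken as 57 in all.

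**The plan's own figure.** Normal approximation, two-sided: n = 2(1.96 + 0.84)²(2/2)² = 15.7, so 16; 16/0.8 = 20. The t-based calculation gives 17; 17/0.8 = 21.25, so 22, within two of the stated 24. With 19 completers per arm, one unadjusted pairwise comparison has 85% power, and 75% with Tukey adjustment over three pairs. The size of 24 is not in question here.

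**Assumptions.** The article gives no distribution shapes. The main scenario is a floor-limited VAS: normal with mean 2 and SD 2 before clipping to 0–10, in every group. Mean and SD are estimated from the sample, and the pre-test is at 5%. Two sets of critical values are used: uncorrected Kolmogorov-Smirnov, and Lilliefors, which allows for the estimated mean and SD.

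**Step 1: how often the check rejects normality (simulated).**

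| Shape and n | Uncorrected | Lilliefors |
|---|---|---|
| Exponential, n = 19 | 3% | 56% |
| Floor VAS, n = 19 | about 0% | 13% |
| Floor VAS, n = 57 | about 1% | 46% |

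**Step 2: how often two visits get different verdicts.** For independent visits with rejection probability p at each, this is 2p(1 − p).
- Per group, n = 19, Lilliefors: 2 × 0.13 × 0.87 = 0.23.
- Pooled, n = 57, Lilliefors: 2 × 0.46 × 0.54 = 0.50.

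The same patients are measured twice, so correlated visits were simulated (20,000 runs per case, Lilliefors):

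| Between-visit correlation | Per group, n = 19 | Pooled, n = 57 |
|---|---|---|
| 0 | 22% | 50% |
| 0.5 | 21% | 42% |
| 0.7 | 20% | 37% |

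With pre-clipping means of 3 and then 2, the figures are about 16% per group and 44–47% pooled, at all three correlations. With uncorrected values in these scenarios, discordance is at most about 1.5%.

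**Step 3: does the check distort error rates?** The two-stage procedure was simulated with 19 per arm and a pooled Lilliefors check, then ANOVA or Kruskal-Wallis. Kruskal-Wallis is an assumption, since the article names no omnibus rank test. For the floor VAS, omnibus type I error is 4.5–4.9%, against 4.7–5.0% for ANOVA alone. For group means 2/2/4, power is 88.3% against 88.7%.

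**Step 4: what a fixed baseline-adjusted model gives.** With 19 per arm and an assumed correlation of 0.5 between baseline and outcome, the residual SD falls from 2 to 2 × √(1 − 0.25) = 1.73. When one group differs by 1.5 points, omnibus power rises from about 64% to about 75%. For 2 points it rises from about 88% to about 95%. Type I error stays near 5%.

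**The case against.** The strongest reply is that the check does almost no inferential damage. Step 3 bears this out, and it stands: a reader might infer inflated false positives from a data-driven choice of test, but the calculation does not show them.

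A reader might also infer that the pre-test has almost no power at this size. That holds for uncorrected critical values with most shapes, not for Lilliefors values, and the article does not say which apply. Nor can near-zero power and frequent switching be claimed together: a check that never rejects leaves ANOVA in place throughout.

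Visit-by-visit classification is permitted, not stated. Speaking of normal or non-parametric variables could equally mean one classification per outcome. How the test is applied could also be left to an analysis plan that is not shown. This stands in part. The between-visit figures then describe what the text allows, but even a single classification lets the data choose between means and ranks. That choice is stated in the article itself.

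The article summarises data by means and SDs in any case, so a crude mean difference stays available, and a group difference at 2 months can be read from either kind of test. It is therefore too strong to say that maintained benefit could not be judged. What would be missing on the rank branch is a confirmatory estimate on the scale used for sizing.

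Finally, the pooled rates assume no treatment effect. With group means 2/2/4 or 2/3/4, the pooled rejection rate falls from about 45% to 19% or 8%. For independent visits, discordance is then 2 × 0.19 × 0.81 = 0.31 or 2 × 0.08 × 0.92 = 0.15. It is smaller but not negligible.

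**Conclusion.** The point holds in a limited form. The article lets a normality test on trial data choose between mean-based and rank-based confirmatory analysis and does not fix how that test is applied. One outcome may therefore be analysed on different scales at the two post-baseline visits, and the rank branch does not estimate the 2-point mean difference behind the sample size.

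The size depends on the unstated critical values. With uncorrected values the check is close to idle in the floor-limited VAS scenario. With Lilliefors values, the two visits disagree in about 20% of trials per group and about 37–50% pooled, for correlations from 0.7 down to 0. The pooled figures are lower if the groups truly differ. All of this rests on an assumed post-treatment distribution that the article does not give. The consequence is a data-dependent and possibly inconsistent effect measure. Worth changing before analysis; not a threat to validity.

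**What to change.** Delete the normality test as a selector of method. For each continuous outcome, name one baseline-adjusted linear model (ANCOVA) for both the post-treatment and the 2-month visit, and report adjusted mean differences with robust or bootstrap 95% confidence intervals. Add one prespecified rank-based sensitivity analysis of the primary pain outcome, run whatever the distribution looks like.

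The strict minimum is to fix one method per outcome for both visits. Baseline adjustment goes further, but it uses data already collected and brings the power gain in step 4 if the assumed correlation of 0.5 is about right. The cost is revised wording and one additional analysis. No patients, visits or measurements are added and no sample size figure changes. The article reports recruitment as ongoing, so on its own text the change could be made before analysis.

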### Ethics and data security

This trial was approved by the Ethics Committee of the School of Medicine of the University of São Paulo (protocol study - 209369/2013). All patients will be asked to provide written, informed consent prior to randomization, using standard forms. This trial is registered in ClinicalTrials.gov (a service of U.S. National Institutes of Health) under the number NCT01778881.

## Discussion

The purpose of this randomized clinical trial is to compare two physical therapy interventions with dental treatment in the management of pain, mandibular range of motion, sleep quality, anxiety, stress, depression, and oral health in individuals with bruxism. The study will support the practice of evidence-based physical therapy for individuals with bruxism. Data will be published after the study is completed.

## Trials status

We are currently recruiting participants.
